## 10 QUALITY CONTROL AND QUALITY ASSURANCE

The medical observations of the prehospital team will be kept on the patient's "medical observation sheet".

The data concerning the study will be reported in the observation notebooks provided for the study, according to good clinical practices, taking into account the different steps of the patient's management in the protocol. Any deviation from the protocol will be reported, as well as the reason for it. The data collection must be exhaustive and will be regularly checked by a clinical research associate (C.R.A.) according to the planned procedures.

The monitoring of the trial will be carried out by CRAs mandated by the sponsor. It will depend on the number of enrolments in the study.

During site monitoring visits, CRAs should be able to consult:

- \* the investigator's binder containing the consents of the participants or their relatives
- \* the data collection books of the patients included
- \* patient medical observation sheets and any other source documents
- \* The hospital information system

The monitoring will check at least the following points:

the existence of patients, the consent process

- \* compliance with inclusion and non-inclusion criteria
- \* the primary endpoint
- \* monitoring and reporting of SAEs
- \* the occurrence of new facts requiring the tabling of an amendment

A written monitoring visit report will be prepared for each visit and kept in the sponsor's documentation.

At the end of the trial, closing procedures will be applied, with all documents and source data filed. Once the final analysis is completed and validated, the entire file and data are sealed and archived according to specific procedures in a secure facility.

In addition, investigators agree to accept quality assurance audits by the sponsor and inspections by the Competent Authorities. All data, documents and reports may be subject to regulatory audits and inspections without prejudice to medical confidentiality.

## 11 ETHICAL CONSIDERATIONS

The sponsor and the investigators undertake that this research will be carried out in accordance with the law n°2004-806 of August 9, 2004, as well as in accordance with the Good Clinical Practices (ICH version 4 of May  1996, and decision of November 24, 2006) and the Helsinki declaration.

The investigator is responsible for the conduct of the trial. He/she agrees to:

- to retain the source data and administrative documents related to the protocol,
- not to include volunteers before receiving official authorizations from the CPP (Ethic Committee) and the ANSM
- to respect the protocol
- to conduct the study in accordance with the moral, regulatory, ethical, and scientific principles that govern clinical research,
- to collect the informed and written consent of each volunteer,
- to report any serious adverse events.

Subjects will be given complete oral and written information about the trial. A letter of information will be given to the patient by the investigator or the physician who represents him/her prior to his/her inclusion in the study. The information letter and consent form will be prepared in triplicate, and one copy will be given to the subject; a copy will be kept by the investigator, who will forward the last copy to the sponsor in a sealed envelope for filing in the permanent trial documentation.

The consent will be signed by the investigator or the physician representing him/her and the patient and/or, if applicable, the trusted support person or a family member.

ANSM authorization and CPP (Ethic Committee) opinion

The sponsor will submit a request to the ANSM to obtain an approval from the CPP (Ethic Committee) before the start of the research, following article L1121-4 of the Public Health Code.

Changes to the protocol

The sponsor alone is authorized to modify the protocol in conjunction with the coordinating investigator.

Substantial modifications are those that have a significant impact on any aspect of the research, in particular on the protection of persons, including their safety, on the conditions of validity of the study, the quality and safety of the products tested, on the interpretation of the scientific documents that support the conduct of the research, or on how the research is conducted.

A request for substantial modification is sent by the sponsor either to the ANSM, or to the CPP (Ethic Committee), or to both of these organizations, as the case may be, for approval. Upon receiving the approval, the amended version of the protocol is sent to all investigators by the sponsor.

A non-substantial amendment to the protocol is a minor change or clarification that does not affect the conduct of the trial. These modifications will not be submitted to the competent authorities but will be agreed upon between the sponsor and the investigator and will be clearly documented (in the study follow-up file).

**12 DATA PROCESSING AND RETENTION OF DOCUMENTS AND RESEARCH DATA**

Data processing will be carried out under the conditions of confidentiality defined by the amended law of January 6, 1978, relating to the French data regulatory agency (CNIL). Data processing will be carried out in accordance with the requirements of the CNIL MR001 reference methodology.

The data concerning this study will be archived for a minimum of 30 years from the end of the research or its early termination without prejudice to the legislative and regulatory provisions in force.

The following documents related to this research are archived in accordance with Good Clinical Practices for a period of 30 years following the end of the research:

\* By investigators:

- The protocol and any amendments to the protocol
- Observation books (copies)
- Source records of participants who have signed a consent
- All other documents and correspondence related to the research
- Original signed informed consents from participants

All of these documents are the responsibility of the investigator for the duration of the regulatory archiving period.

\* By the sponsor:

- The protocol and any amendments to the protocol
- The original observation books
- All other documents and correspondence related to the research
- A copy of the signed informed consents of the participants in a sealed envelope
- Documents related to severe adverse events

All of these documents are the responsibility of the sponsor for the duration of the regulatory archiving period.

No removal or destruction will be made without the agreement of the sponsor. At the end of the regulatory archiving period, the sponsor will be consulted for destruction.

All data, documents, and reports will be subject to audit or inspection.

The study site investigators and members of their research team will make a reasonable effort to ensure the research subjects' confidentiality.

# Prehospital Lyophilized Plasma for Trauma-Induced Coagulopathy in Patients at Risk

## for Hemorrhagic Shock: A Multicentre Randomized Open-label Trial.

### The PREHO-PLYO Study.

## 15 LIST OF AMENDMENTS

| List of the PREHO PLYO Study protocol amendments from 2016 to 2019                                  | Ethics Committee |
|-----------------------------------------------------------------------------------------------------|------------------|
| Simplification of the inclusion criteria : Shock Index (Heart Rate/ Systolic Blood Pressure) | 04/26/2016       |
| Addition of 4 Investigators                                                                         | 04/26/2016       |
| Prehospital Point of Care use by Advanced life support teams                                 | 01/10/2017       |
| Addition of 2 Investigators (Lyon, Annecy Hospital)                                                 | 01/31/2017       |
| Addition of Consent Details (for the relative of a dead patient)                             | 01/31/2017       |
| Addition of 5 Investigators (SMUR 75)                                                               | 01/04/2019       |
| Shock index change from 1.3 to 1.1                                                           | 11/03/2017       |
| Addition of 1 Investigator (SAMU 94)                                                                | 01/30/2018       |
| Addition of 2 Investigators (SAMU 13)                                                               | 11/08/2018       |
| Additional of 3 investigators (BSPP)                                                                | 11/08/2018       |
| Extension of the study to September 2019                                                     | 11/08/2018       |
| Change of coordinator investigator (HEGP hospital)                                                  | 11/08/2018       |
| Withdrawal of 1 investigator (Dead)                                                                 | 01/15/2019       |
| Change of coordinator investigator from [name] to [name]                                     | 08/16/2018       |
| Clarification of consent in emergency situation                                              | 03/12/2019       |
| Change of primary endpoint from delta-INR to INR                                             | 07/12/2019       |
| Addition of Brest center (SAMU 29)                                                                  | 01/15/2019       |

**Trial registration number**

- DCSSA 2014RC04
- ID RCB 2015-A00866-43

**SAP Version**

- Version SAP of May 27, 2019

**Protocol Version**

- This document has been written based on information contained in the study protocol Version dated May 27, 2019

**SAP revisions**

- First simplification of the inclusion criteria ( Date changed, 04/26/2016)
  - Deleting blood pressure and heart rate threshold values and using the Shock Index (ratio of heart rate to systolic blood pressure) with a threshold at 1·3
- Second simplification of the inclusion criteria (Date changed, 11/03/2017)
  - Change of the shock index threshold from 1·3 to 1·1
- Modification of Primary Endpoint ( Date changed, 07/12/2019)
  - Deleting "INR differential between pre-and in-hospital values" and replacing with the "INR value at hospital arrival."

The SAP versions were amended at the same time as the protocol

## 1575 **16.1   Background and rationale**

- 1576
- 1577                   ▪   Acquired failures of hemostasis during severe bleeding promote and maintain bleeding.
- 1578                   Lyophilised plasma (FLYP) has been administered many times in the military setting, but only
- 1579                   non-randomized observational studies have been performed in this context. Furthermore, it has
- 1580                   never been used in the civilian prehospital setting. Therefore, there are no prehospital studies
- 1581                   available that have compared the currently recommended treatment of hemorrhagic shock
- 1582                   without FLYP versus with FLYP.

1583

## 1584 **16.2   Objectives**

- 1585
- 1586                   ▪   Hypothesis
  - 1587                   ●   The null hypothesis is that there is no difference in the occurrence of trauma-induced
  - 1588                   coagulopathy between the standard and plasma groups. The alternative hypothesis is
  - 1589                   that there is a difference between the two groups.
- 1590                   ▪   Objectives
- 1591                   ▪   Principal
  - 1592                   ●   To show the effectiveness of FLYP administered prehospital during the management
  - 1593                   of hemorrhagic shock of traumatic origin, on the occurrence or treatment of post-
  - 1594                   traumatic coagulopathy.
- 1595                   ▪   Secondary
  - 1596                   ●   Feasibility of FLYP administration in the prehospital setting
  - 1597                   ●   Show that FLYP improves fibrinogen levels
  - 1598                   ●   To show that the contribution of FLYP decreases the transfusion needs (Red Blood
  - 1599                   Cells, plasma, coagulation factors, platelets)
  - 1600                   ●   To show that the contribution of FLYP decreases the length of stay in intensive care
  - 1601
  - 1602                   ●   Compare mortality between the two groups until D30
  - 1603                   ●   Validate the safety of plasma transfusion in the prehospital setting.

## 1604 **16.3   Trial design**

- 1605
- 1606                   ▪   The trial is a Multicenter, randomized, open-label controlled study. From the prehospital phase,
- 1607                   the FLYP+ group receives the reference treatment, both symptomatic and etiological, as well as
- 1608                   the administration of FLYP. The control group (FLYP - group) receives the reference treatment,
- 1609                   both symptomatic and etiological, but no administration of FLYP, which is replaced by saline.
- 1610

## 1611 **16.4   Randomization**

- 1612                   ▪   Randomization assigns either the FLYP treatment combined with the usual treatment or the
- 1613                   usual treatment alone.
- 1614                   ▪   CTSA randomizes study treatments in blocks of 2 boxes (one with FLYP, one without).

- 1615                   ▪ The treatment boxes are numbered in ascending order from 1 to 140.
- 1616                   ▪ The CTSA and the EFS will distribute the numbered boxes to the prehospital investigating
- 1617                   centers as they are included (at the request of the centers) and by ascending order from 1 to 140.
- 1618                   Only one pack will be available in each ALS vehicle at the time of patient management.
- 1619                   ▪ The randomization list will be maintained by CTSA and SSA.

## 1620   **16.5   Sample size**

- 1621                   ▪ A previous observational study in a military setting (reference 18 in the study protocol) in
- 1622                   patients with traumatic hemorrhage of "before-after" FLYP administration with Prothrombin
- 1623                   Time (PT) as endpoint showed a significant improvement in PT after FLYP. A total of 124
- 1624                   patients were required to observe a statistically significant difference.
- 1625                   ▪ After the change in the primary endpoint, the sample size was revised and recalculated. Given
- 1626                   that we could not increase the number of patients due to logistical, organizational, and financial
- 1627                   reasons, we calculated the power we could achieve with the same number of patients.
- 1628                   ▪ We calculated that a sample size of 30 patients with coagulopathy would be appropriate in each
- 1629                   group to detect a mean difference of 0.3\* in international normalized ratio values at hospital
- 1630                   admission, assuming a standard deviation of 0.4, with a two-sided type I error of 0.05 and a
- 1631                   power of 80%. Assuming an incidence of coagulopathy of 50% † , this calculation results in 60
- 1632                   patients per group. With an a priori assumed loss of 10% because of lack of informed consent,
- 1633                   we round the size of each group to 70 for a total of 140 patients.
- 1634                   ▪ The concession to the original calculation is essentially a 0.1 increase in the standard deviation
- 1635                   and a power loss from 90% to 80%.
- 1636                   ▪ We anticipate calculating the number of subjects to compare two medians in case the primary
- 1637                   endpoint's distribution is not Gaussian. Indeed, let's consider a median difference of 0.3 in
- 1638                   international normalized ratio values instead of a mean difference. The sample size should be
- 1639                   25 patients with coagulopathy in each group, under the same assumptions of alpha (0.05) and
- 1640                   beta (20%) risk.

1641                   \*This intervention effect is only based on one thesis, and is not based on previous valid studies  
 1642                   because we could not identify such studies in the literature. We pragmatically chose the anticipated  
 1643                   effects based on one observational study and clinical judgment. Therefore, a difference of 0.3  
 1644                   observed in a time frame as short as that of a prehospital intervention seemed to be the minimum  
 1645                   clinically significant difference relevant to us.

1646                   † This incidence is based on an international normalized ratio level threshold of 1.2 and is partially  
 1647                   explained by a significant increase in severity in injured patients when the study protocol was  
 1648                   written.

## 1649   **Framework**

- 1650                   ▪ The outcomes are testing for the superiority hypothesis.
- 1651                   ▪ There are no plans to conduct an interim analysis.

## 1652   **Timing of final analysis**

- 1653                   ▪ All outcomes will be analyzed collectively when the required number of inclusions across the
- 1654                   standard care vs. plasma arms, and follow-up of 30 days, have been reached.

## 1655   **Timing of outcome assessments**

- 1656                   ▪ The schedule of study procedures is given in paragraph 3.3.5 of the protocol.
- 1657                   The start time for each calculation is the participant's date of inclusion.

1658 **Confidence intervals and P values**

- 1659                   ▪ All statistical tests will be 2-sided and performed using a 5% significance level and 95% two-
- 1660                   sided confidence intervals.
- 1661                   ▪ No adjustment for multiplicity is planned
- 1662                   ▪ 95% two-sided confidence intervals

1663 **Adherence and Protocol deviations**

- 1664                   ▪ Protocol deviations are defined as:
- 1665                             ● Enrollment without meeting inclusion criteria
- 1666                             ● Incomplete or lack of patient consent
- 1667                   ▪ The number (and percentage) of patients with major and minor protocol deviations will be
- 1668                   summarized by treatment group, with details on the type of deviation. Protocol deviations will
- 1669                   be screened for in the intention-to-treat population.

1670 **Analysis populations**

- 1671                   ● The people analyzed will be:
- 1672                             ▪ for the safety outcome: all the randomized patients (intention-to-treat population).
- 1673                             ▪ for the primary and secondary outcomes: all the randomized patients except those who have an
- 1674                             exclusion criterion (modified intention-to-treat population)
- 1675                             ▪ for a sensibility analysis for the primary outcome: all the randomized patients except those who
- 1676                             have an exclusion criterion and those who finally have no bleeding after hospital assessment
- 1677                             (per-protocol analysis)

1678 **16.6 Trial Population**

- 1679                   ● Screening data
- 1680                             ▪ The number of patients screened will be reported for each investigating center. The flow chart
- 1681                             will note the total for all centers
- 1682                   ● Eligibility
- 1683                             ▪ The Consort Flow chart will report the number of patients eligible and not eligible due to an
- 1684                             exclusion criterion (paragraph 4· in the protocol)
- 1685                   ● Recruitment, Withdrawal and Follow-up
- 1686                             ▪ The "CONSORT" diagram will report the number of people screened, eligible, consented,
- 1687                             randomized, receiving their allocated treatment.
- 1688                             ▪ The level of consent withdrawal will be tabulated as consent to continue follow-up and data
- 1689                             collection
- 1690                             ▪ Timing and number of patients lost to follow-up will be presented in a Kaplan-Meier Diagram.
- 1691                             ▪ The numbers of losses to follow-up will be summarized per treatment arm
- 1692                   ● Baseline patient characteristics
- 1693                             ▪ Patients will be described with respect to age, sex, comorbidities, type of injury, mechanism of
- 1694                             injury, anatomic localization of trauma, time response of advanced life support teams, vital
- 1695                             status at the point of injury (blood pressure, heart rate, shock-index, oxygen saturation),
- 1696
- 1697

1698 prehospital biological measures (Prothrombin time and INR value, hemoglobin and lactic acid  
1699 concentrations), body temperature, basic life support therapeutics, advanced life support  
1700 therapeutics, cumulated crystalloid volume, cumulated plasma volume, prehospital red cell  
1701 units transfused, vital signs on arrival at the intensive care unit (blood pressure, heart rate,  
1702 shock-index, injury severity score, traumatic brain injury confirmed with CT scan, laboratory  
1703 values - hemoglobin, platelets, lactic acid, base excess)

1704

- 1705     ▪ The description will be reported separately for the two randomized groups. Categorical data will
- 1706     be summarized by numbers and percentages. Continuous data will be summarized by mean, SD,
- 1707     and range if data are Gaussian, and median, IQR, and range if data are skewed. Tests of
- 1708     statistical significance will not be undertaken for baseline. Instead, the clinical importance of
- 1709     any imbalance will be noted.

1710

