|                                                                | 
 
- A person deprived of liberty
 
- Person subject to a safeguard of justice measure
 
- Unrectified Legionnaire
 
- Pregnancy
 
- History of known allergies to amotosalen and psoralens
 
- Administration of coagulation factors other than FLYP
 
- Patient in cardiac arrest before the arrival of professional rescuers
 
                                                                                                                                                                                                                                                                                                                                                                                                                                                                                                              |
| Exclusion criteria                                      | 
 
- Non-usable blood sample
 
- Refusal to participate by the patient
 
                                                                                                                                                                                                                                                                                                                                                                                                                                                                                                                                                                                                                                                                                                                                                                                                          |

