### 3.9 Data to be collected directly in the CRF (source data)

#### **Data collected in prehospital:**

Age,

gender

Circumstances

- ALS team delays (departure time, presentation time)
- Description of lesions, their type, and the organ injured
- Clinical parameters at ALS team arrival (HR, BP, RR, SpO2, Temperature, Hemoglobin) and their time of collection
- TREATMENT administered (FLYP or normal saline), and adverse reaction to administration (e.g., erythema), time of administration
- Filling performed: nature of products, quantity, time of administration
- Use of amines: name, dose (before/after FLYP or normal saline administration), time of administration
- Use of tranexamic acid or blood-derived medication (fibrinogen, prothrombin complex, etc.): dose, time of administration.
- Type of ventilatory support: High concentration mask, IOT-VM (FiO2 and ventilatory parameters noted), time of ventilatory management
- Chest tube +/- autotransfusion (quantity, Hemoglobin)
- Possible immobilizations, application of tourniquet or hemostatic dressing, site of tourniquet, time of application
- Transport time to the hospital
- Death before admission to hospital, date and time of death

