### **4.3 Exclusion Criteria**

- Patients who did not receive the final blood sample (required for the primary endpoint)
- Refusal to participate by the patient

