## **8.7 Patients included in the analysis**

Analysis populations will be :

- in intention-to-treat for the safety outcome (ITT: taking into account all randomized patients)
- in modified intention-to-treat analysis for the primary outcome (mITT: taking into account all randomized patients except those for which the eligibility criteria were not met)
- in Per-Protocol (PP: taking into account patients randomized but excluding the patients for which the eligibility criteria were not met and those who were declared free from any haemorrhagia after the hospital check-up.

All statistical analyses will be performed with STATA® software 14.0 or an updated version for Windows (STATA CORP LLC, College Station, Texas, USA).

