## 1774   16.8   Missing data

- 1775                   ▪ Missing data will be processed by multiple imputation.
- 1776                   ▪ Invalid data will be considered missing.
- 1777                   ▪ Multiple imputation procedures will be performed on the data of patients involved in the
- 1778                   modified intention-to-treat analysis (i.e., full ITT except for the patients who have an exclusion
- 1779                   criterion). We will address the issue of missing data using the state-of-the-art multiple
- 1780                   imputation techniques, including all analysis variables, under the assumption that missing
- 1781                   values are missing at random. We will use the MI impute chained command, generate a number
- 1782                   of imputed datasets depending on the fraction of missing information. Analyses run on each
- 1783                   dataset will be pooled according to Rubin's rules. The multiple imputation diagnostic plots will
- 1784                   be reported for the variables with the highest missing rate. We will compare the distributions of
- 1785                   the observed, imputed, and completed values. We will use the kernel- Epanechnikov density

1786 estimator for continuous variables and a histogram for categorical variables. We will use  
1787 Kolmogorov- Smirnov statistics to compare the observed with the imputed distributions of each  
1788 continuous variable in imputed variables. The null hypothesis (i.e., observed and imputed data  
1789 follow the same distribution) is rejected at  $P<0.05$ . The imputed results will be reported as the  
1790 main results because they are similar to the complete case analysis estimates.

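### Read literally, the SAP's modified ITT set removes patients with no arrival sample, including pre-hospital deaths, from 30-day survival, and it conflicts with protocol 8.7

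*Combined protocol and SAP*

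**What the plan says.** - SAP 16.5, Analysis populations, sets the population "for the primary and secondary outcomes: all the randomized patients except those who have an" "exclusion criterion (modified intention-to-treat population". Only the safety outcome uses all randomised patients.
- SAP 16.6 points to the protocol for these criteria: "exclusion criterion (paragraph 4· in the protocol".
- Protocol section 4 separates non-inclusion criteria (4.2) from exclusion criteria (4.3). Section 4.3 has two items: refusal, and "Patients who did not receive the final blood sample (required for the primary endpoint". The Summary words the sample item differently: "Non-usable blood sample".
- Protocol 8.7 defines the set as "mITT: taking into account all randomized patients except those for which the eligibility criteria were not met". It assigns this set to the primary outcome and names no population for the secondary outcomes.
- SAP 16.7 lists 30-day survival as a secondary outcome, and the SAP counts time from inclusion, which is before hospital. The case report form (protocol 3.9) records "Death before admission to hospital, date and time of death".
- SAP 16.7 plans to impute the primary outcome within the modified ITT set and compare the result with complete cases. SAP 16.8 defines the imputation set as "modified intention-to-treat analysis (i.e., full ITT except for the patients who have an exclusion" criterion.

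**The concern.** A patient has an arrival sample only if they reach hospital alive and blood is drawn there. Both happen after randomisation, and the first can be affected by the treatment, which is given in the field and in transit. Restricting an analysis to patients with a sample therefore selects on an event that treatment may change.

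For 30-day survival, the restriction removes deaths from the period in which plasma is given, although those deaths are recorded with date and time. For INR, it removes patients who are likely to be among the sickest, possibly in different proportions by arm. In addition, two definitions of one analysis set, in an open-label trial, leave the denominators of the primary and survival analyses open to choice after the data are seen.

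**Working it through.** **1. Follow one patient through the definitions.** Take a patient who met all eligibility criteria, was randomised, received study treatment and died in transit.

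| Source | Rule | This patient |
|---|---|---|
| Protocol 4.3 | No final blood sample is an exclusion criterion | Meets it |
| SAP 16.5, primary and secondary outcomes | Remove anyone with an exclusion criterion | Out of INR and out of 30-day survival |
| Protocol 8.7, primary outcome | Remove only eligibility failures | In |
| SAP 16.5, safety outcome | All randomised | In, but the SAP safety endpoint lists thrombosis, allergy, TRALI and TACO, not death |

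Consent does not force the removal: protocol 4.7 keeps the data of patients who die before they can consent.

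**2. What is left to impute.** Once unsampled patients are removed, arrival INR can be missing only where a sample was drawn but gave no valid result (SAP 16.8 treats invalid values as missing). The Summary's wording would remove those patients too.

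**3. Survival, assumed rates.** The documents give no pre-arrival death rate. Assume early death of 10% control and 5% FLYP, then 25% mortality after arrival in both arms.

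- Control, all randomised: 0.10 + 0.90 × 0.25 = 32.5%
- FLYP, all randomised: 0.05 + 0.95 × 0.25 = 28.75%
- True difference: 3.75 points
- Restricted set: 25% v 25%, difference 0

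**4. Survival, assumed counts near the protocol's own mortality.** Protocol 7.2.2 puts mortality at around 50%. Take 70 per arm.

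- Early deaths 2 FLYP and 7 control, 28 later deaths in each arm. All randomised: 30/70 = 42.9% v 35/70 = 50.0%, difference −7.1 points. Restricted: 28/68 = 41.2% v 28/63 = 44.4%, difference −3.3 points.
- The same early deaths with equal true mortality, 35/70 in each arm. Restricted: 33/68 = 48.5% v 28/63 = 44.4%, a spurious +4.1 points.

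So the restriction can shrink a true difference or create a false one, and the direction depends on the early-death split.

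**5. INR, extreme assumed scenario.** Simulate 66 per arm with INR = 1 + gamma(shape 1.2, scale 0.3) and no treatment effect. Remove the highest 10% of control values and the highest 4% of FLYP values. FLYP then appears higher by about 0.04 in the mean and 0.02 in the median. Against the target of 0.3, these are 0.04/0.3 = 13% and 0.02/0.3 = 7%. In this scenario the Mann-Whitney false-positive rate rises from 5% to about 12%.

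**6. Sample size.** The plan's figure reproduces. For a difference of 0.3, SD 0.4, two-sided 5% and 80% power, n = 2(1.96 + 0.84)²(0.4/0.3)² = 28 per group. The t-test version gives 29, and dividing by the Mann-Whitney efficiency of 0.955 gives 30.3; the plan states 30. The 10% allowance is for lack of consent only: 70 × 0.9 = 63 per arm, or 31.5 with coagulopathy at 50%, giving power of about 84%. Losing a further 7 per arm leaves (63 − 7)/2 = 28 and 80% power. Losing 10 leaves 26.5 and 78%. Loss of power is a minor matter; selection is the main one.

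**The case against.** The strongest reply is that the SAP never mentions the arrival sample. Its only pointer covers the whole of protocol section 4 and speaks of patients who are not eligible, so an exclusion criterion may simply mean ineligibility. On that reading the SAP agrees with protocol 8.7, pre-hospital deaths stay in, and the detailed plan to impute the primary outcome has something to work on. This reading is possible. A reader might therefore go too far in stating as settled that the SAP drops every unsampled patient. The text supports only that this is the literal result. But the milder reading does not remove 4.3 or the Summary, which still list the sample as an exclusion criterion.

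Three further inferences are tempting and not supported:

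- **That nobody left in the set can lack an arrival INR.** Under 4.3 a patient can be sampled without a valid result. Only the Summary's wording closes that gap.
- **That these deaths disappear from the trial's reporting.** Adverse events are presented by arm, the safety population is all randomised patients, and the CONSORT diagram counts everyone randomised. None of this, however, returns the deaths to the Kaplan-Meier curves or the log-rank test.
- **That the primary result is badly biased.** The INR scenario requires the unsampled patients to be exactly those with the highest values, and FLYP to more than halve early death without affecting INR. Patients in cardiac arrest are not included, which may also keep early deaths few.

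**Conclusion.** Wrong as written. Protocol 4.3, protocol 8.7 and SAP 16.5 do not define one population, and the literal SAP rule makes 30-day survival conditional on reaching hospital and being sampled. The finding about the text rests on the definitions alone and needs no numerical assumption.

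The size is unknown, because the number of deaths before arrival is not given. Under the assumed rates a true mortality difference of 3.75 points disappears; under the assumed counts one of 7.1 points falls to 3.3, or a false one of 4.1 appears. For INR even the extreme scenario shifts the estimate by only about 0.02 to 0.04, although it would also raise the false-positive rate. The firm ground is the survival comparison and the conflicting denominators, not a large bias in the primary result.

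**What to change.** 1. Delete the missing or unusable final sample as a population exclusion in protocol 4.3 and the Summary. Use one mITT definition in 4.3, 8.7 and SAP 16.5, and carry it into 16.8: all randomised patients except those shown by pre-randomisation data to be ineligible and those whose data may not be used.
2. Analyse 30-day survival in that set, from inclusion, with pre-hospital deaths counted as events.
3. For arrival INR, apply the planned imputation to patients who reached hospital without a valid INR. As a sensitivity analysis only, add a worst-rank Mann-Whitney test with death before sampling as the worst rank. Report it as a death/INR composite, since it answers a different question from the primary analysis.
4. Do not score pre-hospital deaths as zero transfusion. Protocol 8.1 counts products given after arrival, so zero would be the best possible value and would favour the arm with more early deaths. Report post-arrival transfusion among patients who reached hospital, with the number of pre-hospital deaths by arm beside it.

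The cost is wording changes in the protocol and SAP and one extra sensitivity analysis. The data are already collected.
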